### Process evaluation

Effectiveness trials are being increasingly complemented by process evaluation, which offers important information to enhance understanding of trial findings. Process evaluation helps to improve understanding of interventions by exploring barriers and facilitators of implementation, perceived mechanisms of effect and context.^40^ Process evaluation will be guided by the Consolidated Framework for Implementation Research (CFIR) to explore:
perceived usefulness of the CaPe interventionbarriers and facilitators of incorporating the CaPe intervention into the everyday work of health professionalssustainability of the CaPe intervention in routine practice.

In-depth, one-to-one interviews will be conducted with four groups of participants:
patients from the intervention arm (*n* = 15–20)carers (*n* = 15–20)all therapists involved in the trialmental health professionals (both psychiatrists and psychologists) (*n* = 10–15).

For participants and carers, maximum variation sampling in terms of different socioeconomic backgrounds, ages, education, gender, geographical areas and clinical profiles (recovery and clinical scores) will be ensured to explore a wide range of experiences. Separate topic guides will be developed by the research team for each group of participants using the CFIR approach. Interviews will be digitally recorded, transcribed verbatim and translated into English. Each interview will last for approximately 60 min. Interviews will be analysed using thematic analysis. Data will be coded by the researchers working independently. A system for regular team meetings will be in place to develop a provisional framework for each set of participants that will be further amended through constant comparison of new data. The final coding framework will be presented to the study team, who will comment on ambiguities and ensure that the framework remains grounded in the data. Analysis will occur in parallel to data collection. The whole team will agree when data saturation has been reached.

### Ethical considerations

Full ethics approval has been received from National Bioethics Committee of Pakistan and the Centre for Addiction and Mental Health (CAMH) Research Ethics Board, Toronto, Canada (REB #138/2021). All members of the research team will comply with the International Conference on Harmonization Good Clinical Practice (ICH-GCP) Guideline. Research staff will be trained in good clinical practice (GCP) and will not begin data collection until the GCP certification is successfully completed. All information provided by the participants will be kept confidential and authorisation will be required prior to access. Patient-identifying information will not be published. Participation in the trial will be voluntary and participants will have the right to withdraw from the study at any time, without giving any reason. Withdrawal from the trial will have no effect on routine care. Informed consent forms will be in the local language for those participants who can read. Participants who are unable to read and write will be provided with verbal information (in the local language) that will encompass all aspects of the participants’ written informed consent form. The consent form will then be signed by the participant and a caregiver will sign alongside. If the participant cannot write, their caregiver will sign alongside the participant's thumbprint. The participant information sheet and the participant informed consent form will include details of the purpose of the study; the opportunity to ask questions; voluntary participation in the study and the right to withdraw from the study at any time, for any reason; and privacy and confidentiality. All participants can decide to participate right away if they want to, or they will be given at least 48 h to read the forms and discuss queries with family or the research team before a decision is made.

#### Safety

We do not anticipate any major risks related to the intervention. However, we acknowledge that potentially vulnerable people with mental illness will be participating in the trial. Some topics discussed or questions asked in the sessions/assessments may cause distress, and in such instances, appropriate support will be provided. We will map available mental health resources, ensuring pathways to care. The research team has considerable clinical and research experience, including the management of difficult situations arising in research interventions and interviews. If any participants recruited to this study experience active suicidal ideation or are subsequently identified as needing treatment that is more intensive they will be appropriately referred for psychiatric evaluation and treatment. Participants in the TAU group identified as needing intensive treatment will be referred to appropriate treatment services after trial completion. Research staff and therapists will be provided with regular supervision throughout the duration of the project. We already have study protocols in place that include details about how to manage difficult situations arising in relation to research, safety and lone working arrangements. In the event of any study-related injury or adverse event, intervention and treatment will be available from medical staff. Any adverse events will be reported to the CAMH Research Ethics Board within the required time frame.

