### Control condition (TAU)

Local medical, psychiatric and family medicine services provide routine care according to their clinical judgement and available resources. Treatment as usual (TAU) will be ascertained by the participant's treating physician. Research staff will record the nature and intensity of TAU delivered to each participant. In current practice, people with bipolar disorder are not routinely referred for any psychological therapies in Pakistan. TAU for the disorder in Pakistan largely comprises pharmacotherapy.

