### Outcome measures

The primary outcome measure is time (in weeks) to recurrence of a mood (depressive/manic/hypomanic/mixed) episode. This will be assessed at each follow-up using the Longitudinal Interval Follow-up Evaluation (LIFE),^29^ an integrated system for assessing the longitudinal course of psychiatric disorders. The assessment will consist of a semi-structured interview, during which an interviewer uses the LIFE to collect detailed psychosocial, psychopathological and treatment information for the follow-up interval. The weekly psychopathology measures are ordinal symptom-based scales with categories defined to match the criteria of DSM-5. Additional secondary measures are listed in Appendix 3.

All scales (both self-report and clinician-rated) will be administered using a tablet, to allow results to be safely and instantly loaded to the study database, with paper versions available if there are technological difficulties. All scales will be translated into Urdu and back-translated into the original language. Most have been used in previous studies in Pakistan, including our pilot.^24^

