### Study procedures

We have seven major recruitment centres, each with multiple out-patient psychiatric units. There are five recruitment sites in Karachi, three in Lahore and one each in Multan, Rawalpindi, Peshawar, Hyderabad and Quetta. Psychiatrists will identify potential participants and offer them information about the study. Those who agree will be contacted by the research team, pre-screened and provided detailed information about the study, including procedures protecting privacy and confidentiality. Potential participants will have a chance to ask questions prior to providing informed written consent. Participants will then undergo a screening assessment based on the eligibility criteria outlined in Appendix 1, followed by the baseline assessment. After that, an independent statistician will check the record of baseline measures and will randomise the participant to one of the two arms of the study. The participant will be contacted by the study coordinator at their recruitment centre within 1 week of randomisation to inform them about treatment allocation. The time and date of sessions will be set based on the participant's preference. Participants randomised to the intervention arm will be offered 12 weekly individual sessions. Each session will last for 60 min. All sessions will be delivered by a trained therapist, who will receive 2 months of training from senior therapists before starting the intervention. Assessments will be carried out at baseline and at 3, 6 and 12 months. The assessment scales will be administered in person and/or via secure videoconferencing software (an alternative to in-person assessment to allow for COVID-19 or travel restrictions) by trained research analysts masked to treatment allocation.

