#### Cost–utility analysis

A cost–utility analysis from healthcare system and societal perspectives will be conducted to establish the cost-effectiveness of CaPE compared with TAU. The treatment groups will be compared with each other at baseline and then at subsequent follow-ups at 3, 6 and 12 months. EuroQol-5D data will be collected at these time points to measure patient quality of life; quality adjusted life-year (QALY) gains between groups will then be estimated and compared at baseline and at the end of the 12-month period. The costs of delivering CaPE and TAU will be collected and will include costs of staff time, including that of therapists and their training to deliver the intervention, resources and equipment used, and any remuneration given to patients for their time. Data on the direct and indirect costs to patients will be collected using a bespoke questionnaire and will include any additional equipment/aids paid out-of-pocket by patients for the sessions as well as time taken off work by the patient and the carer (if any) to attend sessions. Additional data regarding health service use and direct costs to the healthcare system will also be obtained using the Client Service Receipt Inventory, completed by both treatment groups at 3, 6 and 12 months. We will use standard published sources for unit costs where available and supplement this with local sources to convert resource use into monetary values. Costs will be adjusted for inflation to 2025 Pakistani rupees using appropriate inflators. To estimate the cost-effectiveness of CaPE, an incremental cost-effectiveness ratio will be calculated, defined as the difference in costs divided by the difference in QALYs between the treatment groups. Standard procedures will be followed for imputation of missing values as well as for analysis of uncertainty and non-normal distributions. Further statistical analysis of costs will be performed to test for statistical significance of results, and bootstrapping will be performed to estimate variability in key parameters. The robustness of each treatment will be shown through 95% confidence intervals around the cost-effectiveness ratio, with sensitivity analyses.

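### Two adjacent sentences in the Safety section conflict on when a TAU participant who needs more intensive treatment is referred, and only the TAU arm has a stated deferral

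*Protocol article*

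**What the plan says.** The Safety section of the protocol article contains two consecutive statements on referral.

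- The first sets a condition that covers everyone in the trial: "If any participants recruited to this study experience active suicidal ideation or are subsequently identified as needing treatment that is more intensive". The stated action is that "they will be appropriately referred for psychiatric evaluation and treatment". It gives no time and does not mention the arm.
- The second concerns the control arm alone: "Participants in the TAU group identified as needing intensive treatment will be referred to appropriate treatment services after trial completion".

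There is no matching sentence for the CaPE arm.

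Other sections bear on the point:

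- Study procedures fixes the visits: "Assessments will be carried out at baseline and at 3, 6 and 12 months".
- Control condition (TAU) describes the care that continues regardless of the trial: "Local medical, psychiatric and family medicine services provide routine care according to their clinical judgement and available resources".
- The Safety section also says that medical staff will treat study-related injuries and adverse events, in either arm, and that separate study procedures exist for difficult situations.
- Outcome measures defines the endpoint: "The primary outcome measure is time (in weeks) to recurrence of a mood (depressive/manic/hypomanic/mixed) episode". The LIFE interview also gathers treatment information for each interval.
- Cost–utility analysis adds service use from the "Client Service Receipt Inventory, completed by both treatment groups at 3, 6 and 12 months".

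**The concern.** A TAU participant who is found at month 3 or month 6 to need more intensive treatment meets the condition of both sentences. Under the first, the natural reading is referral once the need is identified. Under the second, referral comes after the trial has ended. Staff at thirteen recruitment sites in seven centres could reasonably act in different ways on the same text.

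Two things are at stake. The first is participant safety: an instruction on referral should not admit two timings for the same person. The second is comparability. If sites follow the second sentence, the research team would refer CaPE participants during follow-up and TAU participants later. Co-treatment would then differ between arms because of a trial rule and not because of the intervention, and the comparison of later symptoms, quality of life, service use and costs would carry that difference.

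**Working it through.** No planned figure is involved, so there is nothing to reproduce. The check sets the two sentences side by side and then works out the delay implied by the visit schedule.

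**Step 1: compare the two sentences.**

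| Element | First sentence | Second sentence |
|---|---|---|
| Who | Any participant, either arm | TAU participants only |
| Trigger | Active suicidal ideation, or a need for more intensive treatment | A need for intensive treatment |
| Action | Referral for psychiatric assessment and treatment | Referral to suitable treatment services |
| Timing | None stated; reads as on identification | After the trial is complete |

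The populations overlap in the TAU arm. The second trigger is essentially the same, apart from suicidal ideation, which only the first sentence names. The action is referral in both. The timing differs.

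**Step 2: look for text that reconciles them.**

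- Nothing limits the second sentence to needs found at the last visit, to a milder level of need, or to an additional offer once the study is over.
- Control condition (TAU) leaves care to local services but is silent on referral by the research team.
- The adverse event provision covers treatment, not the timing of these referrals.
- Data management and monitoring gives the Data Safety and Monitoring Committee an advisory role on whether the trial should continue. It does not set a referral rule.

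None of these settles the timing.

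**Step 3: the delay implied by the second sentence.** Inputs are the visits at 3, 6 and 12 months (Study procedures). The assumption is that trial completion is the participant's own 12-month visit.

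- Need found at month 3: 12 − 3 = 9 months.
- Need found at month 6: 12 − 6 = 6 months.
- Need found at month 12: 12 − 12 = 0 months.

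If trial completion means the end of the whole trial, the wait is longer by an amount that the document does not give. The first sentence states no wait for the same person.

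**Step 4: which outcomes could be touched.**

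- Where the need arises because a mood episode has already recurred, the primary event has been counted. Later co-treatment cannot change it.
- Where the need arises before any recurrence, a difference in referral could influence the time to recurrence.
- Mood scores (YMRS, HRSD-17), EQ-5D and CSRI continue to be collected up to month 12 under the Appendix 3 schedule. These, and the QALYs and costs built on them, are the main places where an arm difference in referral would show.

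The document gives no rate for the need for more intensive treatment and no effect of referral on any outcome, so neither the number of participants affected nor the size of a bias can be computed.

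**The case against.** The best case for the plan has several parts.

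- **The two sentences may be compatible.** The first gives no explicit time, and the services named in the two are worded differently. Staff could refer during follow-up and again at the end, with the second sentence meant as an extra post-trial provision for controls. This is possible, and nothing shows that arm-dependent referral was a deliberate choice. But the text does not say so, and the plain reading of the second sentence is a deferral. The possible benign intention is a reason to clarify; it does not remove the conflict.
- **Care is not withdrawn.** A reader might infer that controls who deteriorate go untreated for months. The document does not support that. Treating physicians continue to provide care, adverse events are treated in both arms, and suicidal ideation is not mentioned in the deferred sentence. This stands, and it confines the point to referral by the research team.
- **Operational detail may sit elsewhere.** The article mentions other study procedures that are not shown, and an article need not repeat them. That would answer a complaint about missing detail. Here the article states two rules, and they disagree.
- **Treatment data are already collected.** LIFE and the CSRI cover treatment and service use, and research staff record the TAU that each participant receives. This stands and makes the data part of the fix small.

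A reader might also try to size the problem from the Sample size section. An exponential distribution with the assumed TAU mean of 21.4 weeks gives 1 − exp(−52/21.4) = 0.912, or about 137 of 150 TAU participants with a recurrence by week 52. That is not a count of people affected. It includes every depressive, manic, hypomanic or mixed recurrence, and nothing in the document equates a recurrence with a need for more intensive treatment. It also assumes a distribution that the section does not state and ignores the 20% attrition allowed for there.

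**Conclusion.** The point holds as an internal inconsistency on referral timing. On their plain reading the two sentences cannot both govern a TAU participant identified during follow-up, and no other section reconciles them. Two premises support this: that the first sentence, which states no time, means referral on identification; and that the second is not limited to needs found at the end, since no limit is written.

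The implied difference is about 9 months for a need found at month 3 and about 6 months for one found at month 6, if trial completion is the participant's own last visit. It is longer if it is the end of the trial.

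The effect on the comparison is conditional: it arises only if sites apply the deferral. It would then fall mainly on secondary and economic outcomes, and on the primary outcome only where the need precedes a recurrence. The document does not support a stronger claim, either that controls are denied care or that the primary result is biased by a known amount. The inconsistency should still be resolved, because it concerns a safety instruction and the correction is cheap.

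**What to change.** The sponsor, the clinical leads and the two ethics bodies that approved the trial should reconcile the two sentences into one statement. It should say explicitly whether handling differs by arm and, if trial completion remains part of the wording, whether that means the participant's last visit or the end of the trial. Which rule applies is a clinical and ethical decision for them; none is proposed here.

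For the analysis, report the referrals made by the research team by arm, using the treatment and service-use data that LIFE and the CSRI already collect. Add a referral date to the case report form if it is not already captured, so that referrals can be placed before or after a recurrence.

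The cost is a clarifying amendment, a notice to sites and at most one date field. The sample size, the primary analysis and the visit schedule do not change.

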### Data management and monitoring

Each participant will be assigned a unique study identification (ID) number and identifying information will be placed in locked cupboards separate from other study data, which will only be accessible to the authorised researchers. Paper copies of assessment tools will all be stored in locked filing cabinets on Pakistan Institute of Living and Learning (PILL) premises. All anonymised data will be stored on encrypted and password-protected computers. We will convene an independently chaired trial steering committee (TSC) to approve and provide oversight of the trial throughout its various stages. The TSC will include the principal investigator, patient representative, local co-investigators, an independent statistician and an independent chair. The patient representative will be a patient volunteer from the Patient Advisory Committee at the local partner organisation, i.e. PILL. The independent statistician and independent chair will be local experts in the design and execution of clinical trials, and will be approached by study investigators. The Data Safety and Monitoring Committee (DSMC) will monitor data and advise the TSC on whether there are any ethical or safety reasons why the trial should not continue. Both committees will meet twice in the first year and then once a year thereafter.

## Discussion

Our own and others’ data from pilot RCTs suggest that psychoeducation in the maintenance phase of bipolar disorder is an effective adjunctive treatment option in low-resource settings, including LMICs.^20,24,41^ We now need to confirm these preliminary findings and extend this pilot work to confirm the effectiveness and cost-effectiveness of CaPE to inform the scalability and sustainability of the intervention in low-resource settings. Psychoeducation as an intervention provides greater insight to the patient and their family/carers, as well as helping to establish a differential understanding of an illness. Lack of information, particularly after diagnosis of a severe mental illness, may render both the patient and their family helpless. A combination of disease-specific (recognition and management of recurrence) and general information (communication skills training, stressor identification and problem-solving skills) is needed to overcome illness-related difficulties. Since psychoeducation is an approach that combines health psychology with psychotherapy, it results in imparting knowledge, while simultaneously equipping the patient and their family with the necessary skills to manage the condition.^42^ Psychoeducation interventions have evolved into sophisticated programmes catering to wide clinical populations, including people with bipolar disorder.^24,43^ Implications of psychoeducation extend beyond maintenance of remission: cost–benefit analyses reveal that as health outcomes improve, healthcare costs are substantially reduced.^44^ Despite these clear benefits, to our knowledge, there are only limited, underpowered studies of psychoeducation from LMICs, including Pakistan. Therefore, the study described here aims to address a scientific research gap on psychosocial interventions for bipolar disorder in low-resource settings such as LMICs. The study could generate convincing data to persuade guideline makers, key opinion leaders, clinicians and patients to include CaPE as a maintenance treatment option for bipolar disorder in Pakistan. It will also enhance information, scientific knowledge, clinical practice and health policy relating to treatment of bipolar disorder in Pakistan and low-resource settings in both low- and high-income countries. Finally, integrating patients and carers into the study strengthens research capabilities in Pakistan by ensuring that future research is oriented towards patient priorities and development of funding bids for collaborative research.
